## Abstract

**Introduction:**

Stroke is the second leading cause of death worldwide, with the greatest burden in low- and middle-income countries (LMICs). Haemorrhagic stroke or spontaneous intracranial haemorrhage (sICH), including intraparenchymal haemorrhage (IPH) and subarachnoid haemorrhage (SAH), has the highest mortality and morbidity. Local management practices for haemorrhagic stroke vary greatly between geographical regions. The Planetary Outcomes after Intracranial Haemorrhage study aims to provide a global snapshot of the patient characteristics, processes of care and short-term outcomes of patients being treated for sICH across high- and low-income settings. It will also describe variation seen in care processes and available resources and time delays to receiving care. A greater understanding of the current state of sICH care is essential to identify possible interventions and targets for improved standards of care in all settings.

**Methods and analysis:**

We describe a planned prospective, multicentre, international observational cohort study of patients admitted to hospital for management of sICH. We will include patients of all ages presenting to hospital with imaging evidence of sICH (IPH, intraventricular haemorrhage and/or SAH). The study will collect patient, care process and short-term outcome data, following patients for up to 30 days (or until discharge or death, whichever occurs first). Any centre globally where patients with sICH are admitted and managed can participate, targeting a sample size of 712 patients. The study will recruit centres worldwide through pre-existing research networks and by dissemination through neurosurgical and stroke conferences and courses. Each participating centre will complete a site questionnaire alongside patient data collection.

**Ethics and dissemination:**

The study has received ethical approval by the University of Cambridge (PRE.2024.070). Participating centres will also confirm that they have undergone all necessary local governance procedures prior to starting local data collection. The findings will be disseminated via open access peer-reviewed journals, relevant conferences and other professional networks and lay channels, including the study website (https://plotich.org/) and social media channels (@plotichstudy).

**Trials registration number:**

NCT06731751.

Strengths and limitations of this studyThe Planetary Outcomes after Intracranial Haemorrhage study will use a collaborative research methodology to provide a global snapshot of current standards in care of patients with spontaneous intracranial haemorrhage (sICH), from the time of admission to the time of discharge or 30 days.The data fields will include both patient and disease characteristics and care process information, providing information on clinical outcomes and healthcare system processes.The study protocol has been developed by an international multidisciplinary panel of experts in brain injury (including stroke and neurovascular surgery), with extensive input from patient and public groups.Key limitations of the study are that only short-term outcomes are collected, and that only patients reaching hospital for treatment of sICH are included, due to the pragmatic study design.

## Introduction

 Stroke is the second leading cause of mortality worldwide and the third leading cause of death and disability combined.^1^ The global stroke incidence is reported at 12.2 million annually and is increasing, with over 80% of cases and associated morbidity and mortality occurring in low- and middle-income countries (LMICs).^1 2^ Stroke is a hallmark non-communicable disease that contributes significantly to the global disease burden and is now disproportionately affecting LMICs undergoing epidemiological transitions. There are now increasing concerns that this burden will continue to grow globally without reciprocated effective interventions.

Haemorrhagic strokes, that is, spontaneous intracranial haemorrhage (sICH), account for approximately one-third of the global stroke burden, with intraparenchymal haemorrhage (IPH) accounting for 27.9% and subarachnoid haemorrhage (SAH) accounting for 9.7% of all strokes, totalling a global estimated incidence of 4.59 million in 2019.^3^ Despite being the minority of cases, IPH and SAH are responsible for the highest morbidity and mortality, and disproportionately affect younger individuals.^3 4^ Geographical variations exist, with IPH being two times as common in LMICs as in high-income countries (HICs) (29.5% vs 15.8%), while SAH is more common in HICs (7.9% vs 19.7%).^1^ However, the true SAH incidence in LMICs is likely to be higher due to underreporting either because a significant proportion of individuals are not reaching hospitals or due to lack of access to neuroimaging to confirm the diagnosis.^5^ Several modifiable risk factors contribute to haemorrhagic stroke, such as hypertension, high body mass index and smoking, as well as environmental factors, such as air particle pollution, meaning that multiple areas for intervention are available.^1^ Better understanding how these factors contribute to disease burden in different settings is important to develop targeted prevention strategies.

Management for sICH is multidisciplinary, with recent evidence suggesting that, in well-resourced healthcare settings, acute care bundles, including rapid access to imaging, blood pressure control, anticoagulant reversal and surgical referral for decision-making, improve outcomes.^6^ Processes of care, including diagnosis, referral and definitive treatment, vary depending on local pathways and resources. Diagnosis of underlying structural causes for the haemorrhage is essential, as this is more likely to require surgical intervention. This requires access to advanced neuroimaging, such as CT/magnetic resonance angiograms or formal cerebral angiograms to identify vascular abnormalities, such as aneurysms, arteriovenous malformations or dural arteriovenous fistulae and cavernomas. However, advanced diagnostics are not always available globally, resulting in diagnostic challenges, which, in turn, lead to missed opportunities for prompt treatment and prevention of disease sequelae.

Surgery (open surgical clipping or endovascular coiling) is often indicated in aneurysmal SAH.^7^ Endovascular treatments, which are becoming increasingly popular around the world, are not yet available in many resource-limited settings.^8^ Even when they are available in resource-limited settings, these interventions are particularly costly, further limiting their availability to only the wealthiest patients in these settings. Surgical clipping, if available, may be the only option in many LMICs.^9 10^ Even when available, delays to surgery can occur due to challenges in access to specialist services and resources, resulting in poorer outcomes than when surgery is performed without delay. Settings where neither treatment option is available are not uncommon in LMICs, and patients are, therefore, managed conservatively.^9^

The role of surgery in IPH remains debated, with significant variation even across high-resource settings.^11^ For example, in the UK, management is primarily conservative under the care of stroke physicians in specialised hyperacute stroke units, whereas in Japan, surgery (often using minimally invasive procedures) is increasingly used.^12 13^ The STICH and STICH II trials showed no benefit of early surgical evacuation but were criticised for strict inclusion criteria.^14^ A recent meta-analysis suggested possible benefits of (minimally invasive) clot evacuation early after symptom onset.^15^ The ENRICH trial showed that minimally invasive evacuation of a supratentorial lobar haemorrhage, when performed within 24 hours, is associated with better functional outcomes than medical management alone.^16^ For infratentorial IPH, such as intracerebellar haemorrhage, surgical evacuation is more common due to the posterior fossa compartment being more susceptible to mass effect.^17 18^

Despite a significant global sICH burden, there is still limited description of its full impact and outcomes, especially in LMICs. Understanding the worldwide variation in sICH-related morbidity, and how this relates to patient and health system factors, is needed to plan services and prioritise context-appropriate interventions.

### Aim

The Planetary Outcomes after Intracranial Haemorrhage (PLOT-ICH) study aims to provide a global snapshot of patient characteristics, processes of care and clinical outcomes of patients being treated for sICH in high-, middle- and low-income settings. It will also describe the variation in available treatment modalities and resources and time delays to receiving care between clinical settings.

### Objectives

Specific objectives are as follows:

estimate sICH case volume to gain insight into variations in epidemiology across world regions;describe differences in patient baseline characteristics, presentation and risk factors;describe the variation in available resources and management pathways for sICH;describe the variation in non-operative and operative management strategies across income settings;describe preoperative, perioperative and postoperative processes of care (including temporal delays to care);identify possible indicators of high-quality care for sICH across income settings;identify gaps in the implementation of best practices along the existing local pathways and care standards;compare short-term clinical outcomes across high-, middle- and low-resource settings.

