### Study setting and population

The study will recruit centres worldwide through pre-existing research networks and collaboratives, developed through the National Institute for Health and Care Research Global Health Research Groups on Neurotrauma and Acquired Brain and Spine Injury. Invitation to participate will also be extended through relevant professional societies and academic groups.

Any hospital admitting patients with sICH worldwide is eligible to participate. A minimum of one case must be submitted by each site during the 30-day chosen study period. At each site, the local team will comprise a local lead, up to two additional data collectors, a data validator and supervising clinician. The study recruitment is planned to run for a total of 12 months (February 2025–January 2026). Eligible patients presenting with sICH over a consecutive 30-day period chosen by each individual recruiting centre during the overall study period will be enrolled. Patients will be followed up until 30 days, death or discharge from hospital, whichever comes first. All data will be submitted to the central study team for inclusion in the final dataset. A minimum sample size of 712 patients will be recruited, as detailed in the Statistical Analysis section below.

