#### Outcome measures

The primary outcome of the study is 30-day mortality or survival to hospital discharge (whichever comes first). Participating centres will be stratified according to income settings, and mortality rates will be compared across cohorts defined by income groups.

Secondary outcome measures include:

perioperative complications, including but not limited to surgical site infections;clinical outcomes other than mortality, measured through:Glasgow coma scale at discharge;modified Rankin scale.Length of hospital stay and intensive care unit stay.

Each unit will be asked to complete a questionnaire on care processes and resources available. This will describe local case load, catchment population and referral pathways, and management frameworks and infrastructure at prehospital and hospital level.

Data will be collected and stored exclusively on a secure web-based system within the Outcome Registry Intervention and Operation Network platform https://orion.net/. This will enable secure data collection, validation and storage in a standard format, which is compliant with the UK National Health Service (NHS) security standards (including the Information Governance Toolkit). All patient data will be recorded and held anonymously. A pilot phase was conducted to assess feasibility prior to rolling out the full study.

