### Limitations

There are limitations worth noting in this study. First, long-term follow-up data are not feasible for this study design. Additionally, this pragmatic study will only include patients reaching hospital for their sICH and, therefore, cannot provide comprehensive data on population-level sICH disease burden. Data validation will ensure robustness of the dataset; however, some missing data are expected in this collaborative study. Finally, this study will not test the efficacy of specific management strategies or novel interventions for patients with sICH.

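### The first objective reads regional epidemiology from case counts at self-selected hospitals, and the stated limitations do not cover centre selection or the share of local cases each hospital receives

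*Protocol article*

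**What the plan says.** All references are to the protocol article.

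- **Objectives.** The first item is to "estimate sICH case volume to gain insight into variations in epidemiology across world regions". Counting cases is the means, and learning about regional epidemiology is the stated purpose.
- **Study setting and population.** "The study will recruit centres worldwide through pre-existing research networks and collaboratives", with further invitations through professional societies and academic groups. The Abstract adds neurosurgical and stroke conferences and courses. Entry is open: "Any hospital admitting patients with sICH worldwide is eligible to participate". There is also a floor on the number of cases per centre: "A minimum of one case must be submitted by each site during the 30-day chosen study period". Each site picks its own 30-day window within a 12-month recruitment period.
- **Outcome measures.** Each unit completes a questionnaire: "This will describe local case load, catchment population and referral pathways".
- **Introduction.** Subarachnoid haemorrhage in low- and middle-income countries is thought to be under-reported, because patients do not reach hospital or cannot be imaged. Management also differs between countries. For intraparenchymal haemorrhage, "in the UK, management is primarily conservative under the care of stroke physicians in specialised hyperacute stroke units", while surgery is used increasingly in Japan.
- **Limitations.** The study "will only include patients reaching hospital for their sICH and, therefore, cannot provide comprehensive data on population-level sICH disease burden". The Strengths and limitations box gives the same reason. Neither mentions how centres come to take part, or what fraction of local cases they receive.
- **Statistical analysis.** Countries are grouped by human development index, and hospital type is named as an example of a subgroup.

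**The concern.** A count of cases at a hospital says something about a region's epidemiology only if one knows which population the hospital serves and what fraction of that population's cases it admits. Centres here volunteer, no region is sampled, and no area has to be covered. A region represented by a few large referral hospitals and one represented by many small general hospitals would show different volumes even if incidence were the same in both.

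At stake is the interpretation of one descriptive objective. If regional volumes were published under that objective as worded, differences in hospital role, access and participation could be read as differences in how common the disease is. The existing limitation would not warn against this, because selection of centres and capture share would remain a problem even if every patient with sICH reached a hospital.

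**Working it through.** **1. The plan's own figure.** The only calculated figure in the article is the sample size. Inputs from Statistical analysis: mortality 30% and 40%, alpha 0.05 (taken as two-sided), power 80%, equal groups. With the pooled-variance formula:

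n per group = [1.960 × √(2 × 0.35 × 0.65) + 0.842 × √(0.30 × 0.70 + 0.40 × 0.60)]² / 0.10² = 356 after rounding up, so 712 in total.

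This reproduces the stated 712. The concern does not depend on it and does not change it.

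**2. What a site's count contains.** For one site over 30 days:

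expected count = incidence × catchment population × (30/365) × capture share

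Capture share is the fraction of cases in the catchment that reach that hospital, are imaged there and are admitted. A regional total adds these counts over whichever centres joined. Setting the sections side by side:

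| Factor | What the article provides |
|---|---|
| Incidence | What the first objective seeks insight into |
| Catchment population | Requested in the site questionnaire |
| Capture share | Referral pathways are requested; the share itself is not among the items the article lists |
| Access to hospital and imaging | Introduction says it is poorer in low- and middle-income countries; eligibility requires imaging |
| Which centres joined | Networks and open invitation; no sampling frame |

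Dividing by catchment gives count / (catchment × 30/365) = incidence × capture share. The questionnaire can therefore remove one factor, but the result is still not incidence. Overlapping catchments and non-participating neighbouring hospitals add to the problem.

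**3. Illustration of the mechanism (assumed inputs, not an estimate).** Assume the same incidence everywhere, 30 per 100,000 per year, and 1,000,000 people around each hospital. Neither figure is in the article. Then 300 × 30/365 = 24.7 cases arise locally per 30 days, and the site expects:

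| Assumed capture share | Expected count |
|---|---|
| 5% | 1.2 |
| 10% | 2.5 |
| 20% | 4.9 |
| 40% | 9.9 |
| 60% | 14.8 |

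The spread is 0.60/0.05 = 12-fold with no difference in incidence. That ratio is simply the ratio of the shares assumed. It shows that volume can move without incidence, not by how much it will.

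**4. The one-case minimum.** If sites with no case drop out and counts are Poisson with mean λ (an assumption), the mean among retained sites is λ / (1 − e^−λ), an inflation of 1/(1 − e^−λ) − 1:

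| λ | Inflation |
|---|---|
| 1 | 58% |
| 2 | 16% |
| 3 | 5% |
| 5 | under 1% |

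Taking the article's expected three to five patients per centre as λ, the effect is small on average. It matters for regions represented mainly by small sites.

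**The case against.** The wording is hedged on both sides. The objective promises insight, not incidence or a regional rate, and the limitation says only that the study "cannot provide comprehensive data on population-level sICH disease burden". Limited insight and incomplete data can coexist. A reader might infer that the two sections flatly contradict each other; the wording does not support that. It is a tension.

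A reader might also infer that regional volumes would mainly show which units joined, or that the centres will be neurosurgical units that see little conservatively managed haemorrhage. The article does not establish either. Any admitting hospital is eligible, stroke conferences are among the recruitment channels, and ward-based and conservative admissions count. The remark on UK practice describes how patients are managed, not which UK units will take part. No capture shares are given, so neither the dominant source of variation nor its size can be stated.

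The article also collects catchment population and referral pathways, and it names hospital type as a subgroup. No analysis of volume by world region is laid out, and scaling and labelling of counts can be left to the analysis plan.

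Most of this stands, and it narrows the point. It does not remove it. The purpose of the objective is fixed in this document, and an analysis plan cannot supply a sampling frame that the design lacks. Catchment data do not identify capture share, and neither limitations passage mentions centre selection.

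**Conclusion.** The concern holds in a limited form. As designed, differences in case volume between world regions cannot be attributed to epidemiology, because incidence is not separable from catchment, capture share, access and participation. The stated limitation covers only patients who do not reach hospital, so it is incomplete and sits uneasily with the first objective.

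The conclusion follows from the recruitment and eligibility rules and needs no numerical assumption. The size of the distortion is unknown and cannot be obtained from the article; the capture-share and Poisson figures above illustrate mechanisms under stated assumptions. The point touches one descriptive objective. The primary mortality outcome, its comparison across income or development groups and the sample size are not affected by it. The change is worth making because it alters what the study may conclude from its counts, but it is not critical to the main analysis.

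**What to change.** 1. Reword the first objective as: *describe sICH case load and subtype mix at participating centres*, and remove the clause about epidemiology across world regions.
2. Where volume is compared, report cases per 30 days per catchment population, using the questionnaire, split by hospital type. Label the result as hospital-based and not a regional incidence.
3. Add two sentences to Limitations: centres are volunteers and not a sample of hospitals in a region, and the share of local cases that each centre receives is unknown.

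The cost is small: the wording of one objective and one limitation, plus a simple rate from data already requested. No new data collection is needed. The price is a more modest claim.

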## Methods and analysis

### Study design

The PLOT-ICH study is a prospective multicentre observational cohort study of patients admitted to hospital for the management of sICH. A multicentre snapshot audit study design was chosen as this offers the opportunity to generate a large, diverse dataset representing many geographical regions, including those often under-represented in research, such as low-resource settings, as demonstrated by examples, such as the Global Neurotrauma Outcomes Study (GNOS), GNOS-Spine and GOAL Trauma studies.^19 20^ This approach encourages collaboration between centres worldwide, and a pragmatic data collection window (30 days) with a short follow-up period per participating centre facilitates contribution while minimising losses to follow-up and attrition related to prolonged data collection periods. These elements contribute to generating real-life data with findings that are impactful globally and delivered in a timely manner.

The core study team, comprising the steering committee and an advisory panel, who were involved in the study design and protocol writing, will oversee the study.

### Study setting and population

The study will recruit centres worldwide through pre-existing research networks and collaboratives, developed through the National Institute for Health and Care Research Global Health Research Groups on Neurotrauma and Acquired Brain and Spine Injury. Invitation to participate will also be extended through relevant professional societies and academic groups.

Any hospital admitting patients with sICH worldwide is eligible to participate. A minimum of one case must be submitted by each site during the 30-day chosen study period. At each site, the local team will comprise a local lead, up to two additional data collectors, a data validator and supervising clinician. The study recruitment is planned to run for a total of 12 months (February 2025–January 2026). Eligible patients presenting with sICH over a consecutive 30-day period chosen by each individual recruiting centre during the overall study period will be enrolled. Patients will be followed up until 30 days, death or discharge from hospital, whichever comes first. All data will be submitted to the central study team for inclusion in the final dataset. A minimum sample size of 712 patients will be recruited, as detailed in the Statistical Analysis section below.

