### Statistical analysis

A formal a priori statistical plan will be produced for data analysis. In short, the primary analysis will comprise statistical descriptive analysis of patient-level variables and the characterisation of processes of care using descriptions of provider profiling data and patient-level process variables.

Country groups will be defined using the human development index (HDI), a recognised index of human development.^21^ The 30-day mortality will be reported for each HDI tier. Further analyses will stratify against other indices of economic development and health. Multivariable logistic regression models will be used to investigate the primary and secondary outcomes. Provider profile summaries will be compared with current evidence-based best practices to identify gaps and associations with care processes and case mix.

There is limited robust epidemiological data on sICH globally across income settings, with mortality rates for hospital cohorts reported between 20% and 33% in HICs and 39% and 62% in LMICs.^22^,^28^ Therefore, an accurate sample size calculation is not feasible. However, taking conservative mortality estimates indicating a 30-day mortality rate for sICH of around 30% in HICs and up to 40% in LMICs, using an alpha value of 0.05 and power of 80% to show a 10% difference between HIC and LMIC settings, a total of 712 patients would need to be recruited. Subgroup analyses will be performed, for example, to describe differences between sICH subtypes or hospital type.

Based on the data and experience from other observational studies with a similar methodology, we would expect that each centre enrols around three to five patients over a 30-day study period.^19^ Therefore, with around 150 recruiting centres from our pre-existing research network, we would expect to meet and exceed the sample size required. Given the nature of this international study, missing values are expected and could affect some participating centres more than others. Patients with at least 70% data field completeness will be included in the analysis. At each site, a data validator, independent from the primary data collectors, will validate accuracy for key study variables to ensure completeness and data accuracy.

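### The one-case minimum per site keeps zero counts out of the case-volume objective: mean volume is biased upward, slightly at the expected 3 to 5 cases per site and more where volume is low

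*Protocol article*

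**What the plan says.** The first item under Objectives is to "estimate sICH case volume to gain insight into variations in epidemiology across world regions". Study setting and population opens participation widely ("Any hospital admitting patients with sICH worldwide is eligible to participate"), has patients enrolled over "a consecutive 30-day period chosen by each individual recruiting centre during the overall study period", and then sets a floor: "A minimum of one case must be submitted by each site during the 30-day chosen study period". The overall recruitment period is 12 months.

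On expected volume, Statistical analysis says "we would expect that each centre enrols around three to five patients over a 30-day study period" and plans "with around 150 recruiting centres from our pre-existing research network".

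There is a second source on volume. Under Outcome measures, each unit completes a questionnaire, of which the article says "This will describe local case load, catchment population and referral pathways". The Abstract (Methods and analysis) assigns that questionnaire to participating centres, alongside patient data collection.

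The article does not say what happens to a site with no eligible case, whether the window must be declared before it opens, or whether zero-case sites count in any denominator. The Limitations section covers patients who never reach hospital and the lack of population-level burden data. It does not cover sites without a case.

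**The concern.** A rule of data collection works against a stated objective. If every contributing site has at least one case, the per-site counts are truncated at zero. Removing zeros can only raise the mean, and the relative error grows as true volume falls. Mean volume would be overstated and contrasts between low- and high-volume groups would shrink.

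The sites most exposed are small hospitals and those with few imaging-confirmed cases. The Introduction itself notes poor access to neuroimaging in low- and middle-income countries, and Study design justifies the snapshot approach by its reach into low-resource settings. If such sites are lost, the description of resources and pathways, also an objective, is selected in the same direction.

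**Working it through.** **The plan's own computed figure.** The only one is the total of 712 for 30% v 40% mortality. With two-sided alpha 0.05, 80% power, equal groups and no continuity correction, n per group = [1.960·√(2·0.35·0.65) + 0.842·√(0.3·0.7 + 0.4·0.6)]² / 0.10² = 356, so 712 in total. It reproduces, and nothing below depends on it. The article computes no figure for case volume.

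**Inputs from the document.** At least one case per site; 3 to 5 cases expected per site per 30 days; about 150 centres.

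**Inputs assumed.** Poisson counts; site means below 3; and, for between-site variation, gamma-distributed site means with shape k = 2 or 1 (negative binomial counts).

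**Poisson.** With true mean m, P(0) = e^(−m), and the mean among sites with at least one case is m / (1 − e^(−m)).

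| True mean m | P(0) | Mean if zeros are removed | Inflation | Source of m |
|---|---|---|---|---|
| 5 | 0.7% | 5.03 | +0.7% | protocol range |
| 4 | 1.8% | 4.08 | +1.9% | protocol range |
| 3 | 5.0% | 3.16 | +5.2% | protocol range |
| 2 | 13.5% | 2.31 | +16% | assumed |
| 1 | 36.8% | 1.58 | +58% | assumed |

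Of 150 sites, the expected number with no case is 150 × 0.0498 ≈ 7 at a mean of 3 and 150 × 0.0067 ≈ 1 at a mean of 5.

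**Contrasts.** Within the protocol's range, a true ratio of 5/3 = 1.67 would read 5.03/3.16 = 1.59, about 4% lower. A true 5:1 ratio would read 5.03/1.58 = 3.2, but that needs an assumed regional mean of 1.

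**Between-site variation (assumed k), zero-case sites lost.** P(0) = (k/(k+m))^k, and the mean among retained sites is m / (1 − P(0)).
- m = 3, k = 2: P(0) = (2/5)² = 0.16; 3/0.84 = 3.57; +19%.
- m = 3, k = 1: P(0) = 1/4 = 0.25; 3/0.75 = 4.00; +33%.
- m = 5, k = 2 and k = 1: P(0) = 0.082 and 0.167; +9% and +20%.

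**Questionnaire case load.** This is not a 30-day count, so the truncation formula does not apply within a site. Only the loss of low-volume sites remains. Under the same gamma assumption, the average true site mean among retained sites is m·[1 − (k/(k+m))^(k+1)] / (1 − P(0)).
- m = 3, k = 2: 3 × (1 − 0.064)/0.84 = 3.34; +11%.
- m = 3, k = 1: 3 × (1 − 0.0625)/0.75 = 3.75; +25%.

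**If a zero-case site moves to another window.** With a constant rate and fresh windows until a case occurs, the count follows the same zero-truncated Poisson, so the first table still holds for that site. The site and its questionnaire stay in the study. Across sites with differing means the overall inflation is then smaller than under drop-out, because drop-out also gives more weight to high-volume sites.

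**The case against.** Several points on the other side are sound.

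- **Size.** A reader might infer that the rule inflates volume by more than half, or turns a five-fold regional contrast into a three-fold one. The document does not support that: both results need a mean of one case per 30 days, which it nowhere gives. Its own expectation is three to five, where the Poisson effect is 0.7% to 5%. The negative binomial figures likewise rest on assumed k. One mean shared by every hospital worldwide is unlikely, so some excess over Poisson is plausible, but its size cannot be taken from the document.
- **The questionnaire.** It gives case load that is not truncated within a site, and the article does not say that enrolled counts, rather than this source, serve the volume objective. This stands. It does not cover sites that leave the study, since only participating centres complete it.
- **Drop-out is inferred.** The article states an obligation without a consequence. A site could move its window, which would keep its resource data. Its zero would still not be recorded.
- **Choosing a window.** A reader might infer from "over a consecutive 30-day period chosen by each individual recruiting centre" that sites can select a period known to contain cases. The study is prospective with consecutive enrolment, and nothing describes choosing a window after the event. That reading is speculation, and no size can be put on it.
- **Analysis plan.** A zero-truncated count model belongs in the separate statistical plan that the article promises, so its absence here is no fault. That plan cannot, however, recover questionnaires from sites that were not retained.
- **Representativeness.** Centres are volunteers from networks, societies and conferences, and Limitations already disclaims population-level burden. Restoring zero-case sites does not cure that.

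**Conclusion.** The concern holds in a limited form. The one-case rule, as written, keeps zeros out of the enrolled counts and pushes mean volume upward, most for low-volume sites. The direction follows from the rule, provided that zero-case sites are either not retained or move to another window, which is the natural reading but is not spelled out.

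At the protocol's expected volume the inflation is about 5% to 0.7%. It becomes material only if some regions average one or two cases per window, or if sites differ markedly in volume, and the document gives neither. The effect is confined to the descriptive objectives on case volume and, if sites are lost, on resources and pathways. The primary outcome and the calculation behind 712 patients are untouched.

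**What to change.** Amend the site rule in Study setting and population so that a site that registers its 30-day window before it opens and completes the questionnaire is retained whether or not a case occurs. Count zero eligible cases as zero in the volume and resource descriptions, and report the number of zero-case sites by region or income group. The one-case minimum can stay as a condition for contributing patient-level data or for authorship.

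The cost is about one sentence in the protocol and keeping questionnaires from sites without cases. The downside is that a few sites add no patient data. With zeros kept, the expected mean among participating sites is the true one for those sites, so the truncation disappears. How far volunteer centres represent their regions remains a separate limitation and should be stated as such.
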